## Abstract

MS clinical features vary between patients. In approximately 60% of cases, cognitive deficits are associated with motor disabilities, with consequences on both walking and maintaining balance and cognitive efficiency. Multimodal programs are very infrequent for MS patients and cognitive rehabilitation is not provided by the Italian health system, which only favors access to motor rehabilitation. Dual-task studies showed how motor and cognitive skills are closely associated. Therefore, physiotherapy exercises may favor an indirect improvement in cognition. The aim of this study is to understand which rehabilitative approach may increase both cognitive and motor efficiency, avoiding the waste of time and resources. In this multi-site single-blind parallel controlled clinical trial, we will compare three rehabilitative approaches: cognitive training, motor training and combined cognitive–motor training. We also aim to evaluate: whether self-perception and objective improvement correspond; the impact of each rehabilitation program on patients’ QoL, mood and self-perception; and long-term effects. A total of 60 patients will be randomly assigned to one of the three treatments for two 45-min sessions/week for 12 weeks. All participants will undergo a complete cognitive, motor, clinical assessment together with mood, self-perception, and QoL questionnaires before, immediately after and 6 months after the training period.

## 1. Introduction

Multiple sclerosis (MS) is a chronic inflammatory, demyelinating and degenerative disease of the central nervous system (CNS): the second-most frequent cause of permanent disability in young adults. The clinical characteristics of MS are extremely variable from one patient to another. In approximately 60% of cases, motor disabilities are associated with cognitive deficits. Concerning motor efficiency, the main sources of disability are walking and maintaining balance [1]. From a cognitive point of view, the main and most frequent emerging deficits concern memory, information processing speed and attention [2]. However, all cognitive functions may be involved even if in a lower percentage of cases. Both motor and cognitive disability emerge even in the early stages of the disease and have a serious impact on patients’ and caregivers’ quality of life. Between them, the most disabling disorders perceived by patients with MS (pMS) are walking deficits, as they most directly affect the ability to efficiently perform even simple daily tasks. For this reason, 65% of pMS consider walking ability rehabilitative intervention a priority [3].

On the other hand, cognitive impairments are often underestimated by pMS, even if they interfere with daily life activities [4,5]. Memory impairment, in example, has a particularly negative impact on social and relational patients’ life [6] and on depression levels. To date, both disease-modifying treatments and specific drug therapies have shown little or no impact on the cognitive deficits complained of by pMS [7,8]. Similarly, motor deficits, once established, are not easily modifiable by pharmacological treatments. We know that rehabilitation strategies improve various functional aspects in pMS [9,10]: an effect probably connected to the structural and functional modifications that occur in the CNS of the treated patients.

The research on rehabilitation programs for MS-related cognitive impairments has become increasingly important: these programs could make patients more autonomous in the management of work and home duties and lighten caregivers’ burden [11,12]. Particular efforts have been directed towards the development of rehabilitation programs for the empowerment of memory: MEMREHAB [13,14], RehaCom [15,16,17] and the modified-Story Memory Technique (mSMT) [18] have shown encouraging results.

The most recent reviews of the literature tried to identify the most suitable rehabilitation tools for each cognitive function in pMS. However, they encountered several difficulties in comparing the results across studies because: some are focused on single-domain rehabilitation, for example the impaired memory function [14], whereas others have set the rehabilitation pathways more broadly, also rehabilitating other connected cognitive functions [17]. This is the case for intensive cognitive training for attention/speeded information processing, executive functions, and memory compared to an aspecific psychological intervention [17]. Furthermore, more recently, interesting results have emerged on the interaction between deficits in cognitive functions and motor impairments [19,20,21]. In particular, it seems that the real disabling effect of MS on patients may be better understood when we consider not only cognitive and motor deficits separately, but also the so called “dual-task effect” describing the mutual interference generated by both deficits each other [21]. This has opened up the possibility that treating cognitive and motor impairments at the same time could be even helpful in enhance the mutual influence of cognition and motor circuits each other.

In this regard, some researchers suggested that a better rehabilitation outcome can be obtained by combining cognitive with motor rehabilitation exercises, than when cognitive and motor functions are treated separately [22]. This makes it difficult to establish which is the most valid rehabilitation approach for the improvement of cognitive deficits (and in particular memory ones) in patients with MS.

In order to increase the possibility of treating cognitive deficits in MS patients, it could be useful to have comparative data on the efficacy of cognitive rehabilitation performed alone with respect to motor rehabilitation alone and with a combined cognitive and motor rehabilitation program.

## 2. Materials and Methods

### 2.1. Aim, Design and Setting of This Study

This study has the following primary objectives:Compare three forms of rehabilitation—cognitive, motor and combined (cognitive–motor)—in three groups of MS patients.Check whether a combined rehabilitation approach can induce a significantly greater improvement on memory efficiency of MS patients, than cognitive rehabilitation performed alone.

Secondary objectives:Evaluate whether self-perception and objective improvement correspond.Evaluate the impact of each rehabilitation program on patients’ overall disability.Monitor the effects of the three rehabilitation conditions after 6 months.

This study will be a single-blind parallel controlled clinical trial, in which each subject will be randomly assigned to a single treatment. The study protocol will be divided into an initial evaluation by standardized tools of clinical, cognitive, emotional, quality of life and functional self-perception state, at time 0 (T0). Subsequently, patients will be assigned to one of the three conditions and will undergo rehabilitation treatment for a total of 12 weeks (two sessions each week). At the end of the treatment, each patient will undergo an overall re-evaluation (T1) with parallel forms of the tools used at T0. After 6 months, all patients will be submitted to a further overall re-evaluation as a follow-up measurement of each treatment (T2). The examiner carrying out pre- and post-treatment evaluations will be different from the one carrying out the rehabilitation process in order to avoid any individual bias. Figure 1 shows the study flowchart.

Patients in charge of both the “Santa Lucia” Neuroscience and Rehabilitation Foundation (Rome) and the “Filippo Turati” Foundation (Rome) will be recruited. All evaluations and rehabilitation training will be conducted at the laboratory and in the rehabilitation sites of the two centers by adequately trained neurologists/physiatrists, psychologists and physiotherapists.

For the 12 weeks following randomization, each patient will undergo one of three rehabilitation programs:Reha 1: is composed by a computerized cognitive rehabilitation training using four sessions of the verbal memory set of the RehaCom program [15,16,17,18,19,20,21,22,23]. Each patient will carry out two 45-min sessions/week for 12 weeks;Reha 2: is composed by a combined rehabilitation program with the use of the four verbal memory sessions of RehaCom together with a motor rehabilitation program. Each patient will carry out one 45-min session of cognitive rehabilitation and one 45-min session of motor rehabilitation each week for 12 weeks;Reha 3: is composed of two 45-min sessions of motor rehabilitation training each week for a total duration of 12 weeks.

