○The California Verbal Learning Test-II (measurement of verbal learning and memory; CVLT-II) [28,29] requires the learning of a 16 words list (made up of 4 words from four different categories) read by the examiner across five trials. After each trial the subject has to recall as many words as possible in any order; the number of words correctly recalled for each trial is recorded. The total Immediate Recall (IR) score is the sum of the words correctly recalled across the five trials, ranging from 0 to 80. After having performed some interference tests the patient has to repeat the previously learned words (Delayed Recall; DR).○The Brief Visuospatial Memory Test—Revised (visuospatial memory test; BVMT-R) [30] consists of three consecutive trials in which the subject views for 10 s a display of six non-iconic figures, arranged in a 2 × 3 matrix. After that the subject has to reproduce each figure in the correct locations on the page. Patient is asked to reproduce the figures again after a 25-min interval without any further exposure to the stimuli. Scoring is based on the subject’s reproduction accuracy and location of each figure [31]. Each figure reproduced can receive 0 to 2 points score [32]. The Immediate Recall (IR) corresponded to the scores’ sum obtained across the three trials while the Delayed Recall (DR) is the score obtained in the 25-min delayed trial. The BVMT-R offers six equivalent alternative forms [33].○The Symbol Digit Modalities Test (information processing speed; SDMT; oral version) features a series of nine symbols, each of which is paired with a single-digit number in a pattern at the top of a sheet. The rest of the page has a pseudo-randomized sequence of these symbols. The patient is asked to say the digit associated with each symbol as quickly as possible in 90 s. The SDMT was originally designed for both written or oral responses, but the expert group recommended oral administration with MS patients to minimize complaints due to upper limb weakness or incoordination. The dependent variable is the total number of correct answers in 90 s [33,34].○The Benton Judgment of Line Orientation test (measures the accuracy of spatial orientation judgments; BJLO) [35] requires subjects to identify the angle defined by two stimulus lines among those reported in a visual series of lines spanning 180 degrees. The dependent variable of the BJLO is the total number of correct answers [33].○The Controlled Oral Word Association Test (measure of phonemic fluency; COWAT) gives subjects three 1-min time intervals each to generate as many words as possible beginning with three different input letters. Given that the subject’s performance is strongly influenced by the efficiency and speed of the search into one’s own lexicon, the COWAT cannot be considered a test of “pure” language. The total score is the total number of words generated in all three tests. Two equivalent alternative forms are available [33].○The Delis–Kaplan Executive Function System Sorting Test (D-KEFS ST) is a composite measure of: concept formation skills, specific problem-solving skills for verbal/non-verbal aspects and ability to explain the abstract ordering of concepts [36]. It is able to explore reasoning, categorization skills, problem solving, abstraction, flexibility of thought and conceptual training skills, and it also provides good validity [37] and adequate reliability [38]. The test involves the presentation of six mixed cardstocks having different perceptual and semantic characteristics. The participant is asked to divide the cards into two groups (categorization), with three cards each, based on objective criteria and to describe the concepts used to generate each categorization (description). Each of the two sets of cards has a maximum of eight types of categories: three based on the semantic meaning of the printed words and five based on the cards’ visuo-spatial characteristics or patterns. The participant has a maximum of 4 min (for each set of cards) to find as many categorizations as possible [39]. The Sorting Score (SS) represents the total number of correct categorizations made by the subject; the Point Score (PS) represents the quality of the description (classifications) made for all the SS.○The Paced Auditory Serial Addition Test in 3 and 2 s versions (measure of working memory; PASAT). It takes 20 min to administer and has adequate sensitivity and specificity (approximately 75% and 90%, respectively) in discriminating compromised patients from intact ones [40,41] In this test the patients asks some digit numbers each 3 or 2 s. He/she is asked to sum the number just said with the previous and say each time the correct sum.

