## 4. Statistics and Outcome

### 4.1. Data Analysis

The sample size has been determined based on an a priori power analysis, using the software G*Power 3.1 [56], with a 0.30 effect size, power of over 0.95, and an alpha level of 0.05, as being sufficient for both repeated measures, within–between interaction Analysis of Variance (ANOVA). The minimum number of participants required is 48 (16 participants for each group), but we have decided to reach a total number of 60 participants (20 participants for each group) in order to avoid possible drop-out effects.

For the purposes of this study, different types of statistical analysis will be carried out using SPSS 18 (SPSS Inc., Chicago, IL, USA) and a significant threshold throughout this study will be set at *p* < 0.05.

Statistical analysis will be of two types:“Within-group” analyses. These statistical analyses will be aimed at evaluating any improvement in patients’ cognitive performance. Within each group of patients, the assessments at T0 will be compared with that at T1 and T2 through a repeated measures ANOVA between the scores of the cognitive assessments. In case of significance, post hoc tests will be carried out to which a Bonferroni correction will be applied with significance set at *p* < 0.016. Similarly, the same analysis will be conducted to compare the levels of anxiety and depression, the self-perception of cognitive deficit and the level of perceived disability.“Between-group” analyses. These statistical analyses will be aimed at comparing the results obtained by the groups at T0, T1, and T2 by performing an ANOVA between the scores of the cognitive assessments. In case of significance, post hoc tests will be performed to which a Bonferroni correction will be applied with significance set at *p* < 0.016. Additionally, in this case, the same comparative analysis will be carried out on the following variables: levels of anxiety and depression, self-perception of one’s cognitive difficulties and level of perceived disability.

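### Within-arm T0–T1–T2 change on the cognitive tests cannot be read as improvement from training: forms are specified for T1 only, COWAT has two listed forms for three visits, and no arm is untreated

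*Protocol article*

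**What the plan says.** - **Forms at T1.** Section 2.1: "each patient will undergo an overall re-evaluation (T1) with parallel forms of the tools used at T0".
- **Forms at T2.** The same section says of the six-month visit only that "all patients will be submitted to a further overall re-evaluation as a follow-up measurement of each treatment (T2". No form is named. The order in which forms are given is not described for any visit.
- **Number of forms.** Section 2.3 says of COWAT: "Two equivalent alternative forms are available". It credits BVMT-R with six equivalent forms. It gives no number of forms for CVLT-II, SDMT, BJLO, D-KEFS ST or PASAT.
- **Analysis.** Section 4.1, under within-group analyses, says "the assessments at T0 will be compared with that at T1 and T2 through a repeated measures ANOVA" and gives the aim as evaluating improvement in cognitive performance. Post hoc tests at p < 0.016 follow if the ANOVA is significant. Between-group ANOVAs at T0, T1 and T2 are planned as well.
- **Role of the outcome.** Section 4.2 makes the cognitive scores primary outcomes, together with gait and balance, considered at T1 and T2.
- **Arms.** Section 2.1 describes three active programmes: cognitive, combined and motor. There is no untreated or waiting arm.

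**The concern.** Patients who repeat a cognitive battery can score higher without any training effect, because they know the task or have seen the items. Parallel forms reduce the second cause but not the first, and the article specifies them for one of the two repeat visits. For COWAT, two forms cannot cover three visits, so on the article's own count one form is seen again at T2.

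This matters because a planned analysis of primary outcomes takes change from T0 as evidence of improvement, and no untreated arm shows how much change to expect from repetition alone. Three uses of within-arm change are exposed:

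- whether objective improvement matches self-perception (a secondary objective), since the objective part would be a change score that contains practice;
- the idea in the abstract and Discussion that physiotherapy alone may improve cognition, which, if judged by change within the motor arm, has no reference for practice;
- persistence at six months. T0–T1 is specified with a parallel form and T0–T2 with an unstated one, so the two within-arm contrasts may differ in form exposure, and a gain that looks kept may be re-exposure.

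**Working it through.** **1. The plan's own figure.** The only related number is the sample size in Section 4.1: effect size 0.30, alpha 0.05, power over 0.95, minimum 48, enlarged to 60 (20 per arm). For the within–between interaction, λ = f²·N·m/(1−ρ). With k = 3 groups, m = 2 measurements and ρ = 0.5 (m and ρ are not stated):

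λ = 0.09 × 48 × 2 / 0.5 = 17.28, with df 2 and 45, giving power 0.958.

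So 48 is reproduced. The present point does not depend on it. It uses only n = 20 per arm and takes ρ = 0.5 as one plausible correlation.

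**2. What a common shift does.** Write the mean of arm g at visit v as μ + τ(g,v) + s(v), where τ is the training effect and s(v) is practice, re-exposure or form difference shared by all arms.

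- Within-arm change from T0: [τ(g,v) − τ(g,0)] + [s(v) − s(0)]. The second bracket cannot be separated from the first.
- Difference between arms g and h at visit v: τ(g,v) − τ(h,v). The shift drops out.
- Group-by-time contrast: the shift drops out for the same reason.

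**3. Size under the planned type of test.** Simulation with 3 arms of 20, 3 visits, normal scores, ρ = 0.5, no training effect, alpha 0.05 and 5,000 runs per row. The shift sizes are assumptions, as the article gives none.

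| Shift at T1 / T2 (SD) | Within-arm ANOVA | Group-by-time | Between arms at T1 |
|---|---|---|---|
| 0 / 0 | 4.8% | 5.2% | 4.5% |
| 0.2 / 0.2 | 13% | 5.6% | 5.0% |
| 0.3 / 0.3 | 25% | 4.9% | 5.1% |
| 0.5 / 0.5 | 61% | 5.0% | 4.5% |
| 0.3 / 0 | 24% | 5.3% | 5.4% |
| 0.5 / 0 | 59% | 4.8% | 5.3% |

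**4. Size for a single paired contrast.** In SD units, SE = √[2(1−r)/20].

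- r = 0.6: √0.04 = 0.20. Non-centrality is 0.2/0.20 = 1.00 or 0.3/0.20 = 1.50.
- r = 0.8: √0.02 = 0.141. Non-centrality is 0.2/0.141 = 1.41 or 0.3/0.141 = 2.12.

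Two-sided rejection from the non-central t with 19 df:

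| Shift, r | at 0.05 | at 0.016 |
|---|---|---|
| 0.2, 0.6 | 16% | 7% |
| 0.2, 0.8 | 27% | 14% |
| 0.3, 0.6 | 30% | 15% |
| 0.3, 0.8 | 52% | 33% |

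The plan runs post hoc tests only after a significant ANOVA and at 0.016. The right-hand column is therefore the relevant one, and it is an upper bound because the gate can only lower it.

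**The case against.** The best case for the plan has five parts.

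- **Order of forms.** A reader might infer that every patient takes the same form first and its parallel second. The text does not say so. An A/B and B/A rotation satisfies it fully, and an article commonly leaves such detail to the full protocol. This stands: silence on order is not a defect in itself.
- **Difficulty of forms.** A reader might infer that the second form is easier. Section 2.3 calls the COWAT and BVMT-R forms equivalent, and nothing shown contradicts that. This also stands: form difference is only a possibility, and practice and re-exposure are the firmer mechanisms.
- **Extent of the shortage.** It is documented for COWAT alone, a fluency test, whereas the specific hypothesis concerns memory. BVMT-R has forms to spare. For the other tests the article gives no count, which does not show that no second form exists. This stands.
- **Randomised comparison.** A reader might infer that the whole T0–T1–T2 evaluation is confounded. It is not. Both primary objectives compare arms, all arms share the stated assessment schedule, and a common shift cancels. The between-arm tests would be affected only if practice differed by arm or forms were distributed unequally across arms, and the article suggests neither.
- **Practice in general.** Uncontrolled pre–post change contains practice in almost any repeated cognitive testing. That is true, but it does not excuse the plan, because Section 4.1 commits to interpreting exactly that change as improvement on primary outcomes.

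**Conclusion.** The point holds for the within-group analyses only. As planned, a significant T0–T1–T2 change inside an arm would not show that training improved cognition, because practice and re-exposure, and possibly form differences, produce the same pattern and no arm is untreated. The within-arm T0–T1 and T0–T2 contrasts may also differ in form exposure, for COWAT in particular.

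Under an assumed shift of 0.2–0.3 SD with no true effect, the false-positive rate of the within-arm ANOVA is about 13–25% at ρ = 0.5. For an ungated paired test at 0.016 it is about 7–33% at r = 0.6–0.8. The higher range of 16–52% belongs to an ungated paired test at 0.05, which is not the planned sequence and should not be used as the headline. The sizes depend on the assumed shift and correlation; the direction does not.

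The randomised between-arm and group-by-time comparisons keep about 5% and are not in question here. This is worth correcting, since it changes what the trial may conclude from within-arm results, but it does not undermine the primary comparison of the programmes.

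**What to change.** **Section 4.1.** State, for all cognitive tests, that within-arm change is descriptive and includes practice, and that treatment effects, including those at six months, are drawn only from between-arm (group-by-time) differences. The rule has to cover every test, because form rotation does not remove practice, and two-form tests still repeat a form at T2.

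**Section 2.1.** State that form order is rotated across patients within each arm, that BVMT-R uses three different forms over T0, T1 and T2, and that two-form tests such as COWAT reuse a form at T2. Rotation balances any form difference over visits and guards against unequal distribution of forms across arms.

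**Cost.** A form-rotation list attached to the randomisation list, a record of which form each patient received at each visit, and a few sentences of text. No extra testing is needed. The real price is weaker within-arm claims: whether motor training improves memory could be judged only relative to the other arms. The rotation has to be in place before patients are tested, since it cannot be added afterwards; the interpretive rule needs only a change of text.
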